### Algorithm 1.0

is a mathematical instrument that determines the required nursing home staff (in number and qualification) based on the number of residents and their care mix within a nursing home. The mean actual and targeted numbers of care interventions and time of provided care (per care dependent in a certain period) can be combined multiplicatively, and required staff numbers can be derived. The primary outcome of applying the algorithm is that for Germany, about 36% more nursing home staff are required to provide adequate needs-oriented care. The input for this calculation was the care mix of all nursing home residents in Germany. The plus of 36% full-time equivalents refers to a care-degree standardized reference nursing home with 100 residents [15]. However, the instrument addresses the overall number of required nursing home staff and specifies it according to the different QL described above. It was found that the lack of staff varies according to the QL of nursing home staff. In the legally given three qualification groups described above, the additional demand for staff in unqualified and semi-qualified nurses was 69,0%. In contrast, for qualified nurses with higher QLs, it was only 3.5% [15].

Based on the study results, the German legislature commissioned a model program to (i) trial and evaluate both measures (increased staffing and work organization), (ii) derive a concept for a national rollout, and (iii) use the findings from the evaluation to parameterize *Algorithm 2.0.* The contracting authority of this model program is the GKV-Spitzenverband (*Spitzenverband Bund der Krankenkassen* – National Association of Statutory Health Insurance Funds).

## Methods and analysis

### Study design and participants

The entire mixed-methods study is planned to run from December 2022 to May 2025 and comprises a complex intervention (running over one year) and its evaluation. The study is designed in four steps. Although in this article, the steps of the study are described consecutively, we should emphasize that in practice, they cannot be considered discrete and independent. The study steps are (i) the development of an initial implementation concept, (ii) the application of the initial concept and the co-creative, iterative development of customized concepts, (iii) a comprehensive summative evaluation, and finally, (iv) the derivation of prototypical concepts for qualification-oriented work organization which considers different starting points of nursing homes and thus offers different development paths for different types of nursing homes, the development of a strategy for the national rollout, and the parameterization of *Algorithm 2.0*.

The intervention consists of increased staffing (based on *Algorithm*
1.0) in 10 nursing homes and restructuring the work organization (intervention group). The central aim of the restructuring of the work organization is qualification orientation. That means that the workflow organization considers the qualifications of the nursing home staff and the resident's care needs to optimize the matching between these parameters (QL-fitting).

Ten matched nursing homes as a control group do not undergo the two intervention measures but participate in the evaluation. Matching criteria are the federal state, number of beds, and ownership. The evaluation assesses (a) the quality of care, (b) the job satisfaction, and (c) the effects on the actual-target differences in number, duration, and QL fit of care provision as defined in step 3 (summative evaluation). QL-fit means that the required QL of the intervention (determined by the complexity of the intervention in interaction with the level of stability of the care situation of the nursing home resident) fits the QL of the nurse. Effects of the intervention concerning (a) and (b) will be measured using a difference-in-difference approach in the intervention and control group nursing home facilities. The difference in difference analysis can be applied when evaluating outcomes associated with healthcare policy implementation. This analysis's beneficial characteristic is the possibility of controlling for background changes [19]. The evaluation compares the pre- and post-intervention differences in outcomes in (a) and (b)—as operationalized below—between the treatment group (10 nursing homes retrieving the intervention) and the control group (10 nursing homes not retrieving the intervention). Endpoint (c) will only be investigated through a pre-post comparison with the intervention group, as the shadowing of the control group was regarded as too resource-intensive.

The study will involve 20 nursing homes in Germany (10 in the intervention group and 10 in the control group), nursing home staff, residents, about 120–150 data collectors (so-called ‘nurse shadowers’), and about 20 assessors and evaluators on behalf of the LTC insurance funds (Medizinische Dienste/medicproof GmbH). The respective work packages describe the participants' involvement in detail.

## Eligibility criteria

Several targeted groups are involved in the study. Nursing home staff must fulfill partially varying inclusion criteria for participation in the different activities. For the survey, they must be involved in the care of the respective nursing home residents and working in the home before the start of the survey. For the shadowing, they must work in the shadowed living area (only in the intervention group). The focus groups must be employed in a participating nursing home from the beginning of the intervention (only in the intervention group). For the competency analysis, they must work in one of the nursing facilities of the intervention group.

Nursing home residents may participate in the survey if they can complete the questionnaire alone or with assistance. A proxy rating will be applied for nursing home residents with cognitive impairments. Participation in the shadowing is possible for nursing home residents if they live in the respective shadowed living area. Terminal residents and residents living in the respective nursing home for less than four weeks will be excluded from the shadowing and the survey.

The inclusion criteria for the shadowers participating in data acquisition (i.e., shadowing) are registration as a qualified (geriatric) nurse and participation in training provided by the study team. There are no further inclusion criteria for the shadowers' survey.

## Recruitment

All nursing homes in Germany that submitted a written statement of interest in participating in the study before a deadline could apply. The study team preselected 30 facilities (concerning the state, number of beds, and ownership). These nursing homes have an average capacity of 76 beds (between 30 and 120 beds), are distributed in all 16 states, and between non-profit, public, and private organizations according to the distribution in Germany. Rural and urban areas were taken into account. After visiting the premises and talking to the staff, the research team forwarded the names of 20 nursing homes to the GKV-SV as the study's funder, which made the final selection of the ten nursing homes for the intervention group. The GKV-SV then concluded a subsidy agreement with the selected nursing home facilities. The nursing homes of the control group are selected by the study team and reviewed by the GKV-SV.

Participation in the study is voluntary and based on informed consent. Participants of the intervention group will be recruited at information events held by the study team in the participating nursing homes. At these information events, the study team aims to inform the staff, the residents, and relatives about the study's aims and procedure, enlist support, and recruit survey participants. Participants for the control group are informed and recruited by the respective nursing home management.

The study is structured into four study steps (Fig. 1).

**Fig. 1 Fig1:**
[figure not shown]
Conceptual framework of the mixed-methods study

## Development of an initial concept

In the theoretical development phase, an initial concept for implementing a qualification-oriented work organization in nursing homes will be developed, starting with a comprehensive national and international literature analysis. Literature will be considered concerning nursing processes, education and training in nursing homes, and theoretical conceptualizations of change processes in organizations. The theoretical basis for the management measures derives from diverse sources in organizational development, personnel development, and change management theories. The management measures will include, for example, monitoring the QL fitting and developing change-process plans. The following components will be combined into the initial concept:i)A nursing process that centers on the care needs of nursing home residents.ii)Education and training measures for different QLs. Formal training courses are planned for QL 4. Training courses are being developed at a low threshold in the QL 1 and 2 work process.iii)A theoretical model for the organizational change process aims for a qualification-oriented work organization. That means a strategy will be developed to assess the QL in nursing homes (actual and target) and adjust the workflow to increase QL fitting.

## Application and co-creative, iterative development of customized concepts

As one single concept cannot be appropriate for all different nursing homes, in the practical trial and customization phase, the initial concept will be further developed into customized and empirically refined implementation concepts. The intervention will begin with applying the initial concept in the ten facilities of the intervention group. The intervention comprises a quantitative and a qualitative component: firstly, increased nursing home staffing based on the previously developed *Algorithm*
1.0 [15]. Secondly, qualitative measures which include organizational (work organization with the aim of QL-fitting) and personnel development (education and training). The iterative development process from the initial to customized concepts starts as the intervention begins. The method applied for further iterative development is formative evaluation. This will be conceptualized as an ongoing participatory process of co-creation by scientists and practitioners from nursing homes.

It starts with depicting the actual status to set an individual starting point for the change process. The assessment of the actual status of the nursing homes comprises:i)Nursing home inspections regarding organizational structures and management of the homes (e.g., infrastructure, care and case mix, organizational concepts), person-related conditions (e.g., staff and nursing home residents), and service provision processes.ii)An assessment for the analysis of competencies on the individual level of the nursing homes’ staff. The analysis of competencies is composed of (i) a self-assessment of competencies for nursing home staff, (ii) a proxy assessment of competencies for management staff, and (iii) a comparison of the results in a personal development meeting. Educational needs can be derived from the comparison results and the agreements made during the talks. The instruments will be developed during the project [20]. The reliability of the self- and proxy assessments will be tested by calculating Cronbach’s alpha.

The formative evaluation process will comprise three instruments to evaluate the concept components' effectiveness, acceptance, and practicability. The instruments are:i)Research diary: Research team members with direct contact with the facilities regularly fill out a standardized form for each nursing home (timely after contact, at least every two weeks). The form contains questions about events, experiences, and information that result from the contact and can provide recommendations for the further development of the concept.ii)Semi-structured expert interviews: Every two weeks, an interview will be conducted with a contact person at the facility (usually the home or nursing service management). Nursing home-specific findings from the research diaries will be used to customize the interview guides and to find solutions co-creatively. In addition to these individual topics, the interviews will concern, e.g., challenges associated with the implementation of the work organization, perceived changes, and the identification of resource-intensive work steps in the implementation.iii)Focus groups: Every two weeks, members of the study team, with direct contact with the facilities, combine the results of the research diary entries and the expert interviews to develop recommendations for further developing customized concepts.

The three elements are repeated continuously for one year, creating an iterative further development and customization process.

## Summative evaluation

The customized concepts will be practiced, refined, and evaluated in the third study phase. The evaluation is planned as a prospective interventional study. In the intervention group, all elements of the data acquisition for the summative evaluation will take place as pre-post-comparison at two points in time (t_0_ before the intervention and t_1_ after the implementation of the changes in organization and staffing) at an interval of one year (note that the shadowing only takes place in one living area per care home). To control for general trends in the dynamic LTC setting and the effects of the revision of Paragraph 113 Section C of the German Social Code, Part 11 (that enacted a new finance of staffing ratios based on *Algorithm*
1.0) 10 nursing homes from the intervention group are matched with ten nursing homes in the control group by state, number of beds, and ownership. The control group undergoes the surveys of the summative evaluation but not the shadowing nor the two intervention measures. A (cluster) randomization was not possible due to the stipulations of the statutory order.

The summative evaluation assesses the effects of the intervention on (i) quality of care, (ii) job satisfaction, and (iii) changes in the difference between (a) the number of provided interventions, (b) the duration of the provided interventions, and (c) the extent of qualification-fitting. Table 2 provides an overview of the data collection methods for the endpoints of the summative evaluation.

**Table 2 Tab2:** Data collection methods for the endpoints of the summative evaluation

Methods and instruments	Operationalization of the endpoints

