The PeBeM data collection method consists of three core elements:Compiling a new assessment of the need for LTC (‘Pflegegutachten’). Within the PeBeM data collection method, experts from the respective assessors and evaluators, on behalf of the LTC insurance funds (i.e., Medizinische Dienste/medicproof GmbH), apply this assessment to gain actual information about the care and health conditions of nursing home residents.Preparing a care intervention plan that follows the day's structure (‘daily intervention planning’, DIP). Scientists from the study team (who also have an exam in nursing) and nurses from the respective nursing homes tailor an individual DIP for every resident. All available and relevant information about the care-dependent person is brought together. The aim of this step is the detailed depiction of the dependents' individual care needs and the planning of all necessary care interventions for the data collection period.The shadowing of the nursing staff. The care provision is observed in the nursing home for about one week. While working, the facility's nursing staff is accompanied by a data-collecting shadower (also qualified nursing staff) on a one-to-one basis. The shadowers document the interventions in real-time and the time needed on an electronic device (tablet computer). The QL of the nursing staff is documented automatically by the software. All interventions planned in the DIP appear on the tablet computer screen and must be documented regarding the actual. The system gives time stamps for the duration of documentation when the shadowers start and stop the observed intervention. If an intervention is not provided, the shadowers document a reason. Additionally, they rate the time spent (in terms of surcharges or deductions) and the number of interventions (that is, they state whether a provided intervention was unnecessary or a necessary intervention was not provided).

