Secondly, paper-based surveys of nursing home residents will be carried out based on the ASCOT questionnaire (Adult Social Care Outcomes Toolkit) on their subjective quality of life [21, 22] and the EQ-5D about health-related quality of life in an evaluated German version [23]. The ASCOT is a care-related quality-of-life instrument with a high construct validity in the given setting [24]. To be able to record changes perceived by nursing home residents due to project-specific interventions (e.g., personnel and organizational changes in the care facility) that are not recorded in the ASCOT and the EQ-5D questionnaires, questions specially formulated for the project are added to the questionnaire (e.g., on satisfaction with organization and communication, perception of turnover of nursing home staff, etc.). In the t_1_ survey, further questions are included to identify the effect of the change, e.g., ‘Has anything changed as a result of the restructuring in the last year?’. For cognitively impaired nursing home residents, a proxy rating is provided via the QUALIDEM questionnaire [25, 26]. In German, the QUALIDEM is available in two versions according to the severity of cognitive decline (measured by the nursing home staff using the Global Deterioration Scale [27]). While QUALIDEM I can be applied in nursing home residents with mild cognitive decline (GDS Stadium 2–6), QUALIDEM II is used in residents with severe cognitive decline (GDS Stadium 7). The subscales of the QUALIDEM are shown in Table 2. The written survey and the proxy rating are planned for all nursing home residents living for at least four weeks in one of the participating nursing homes in both the intervention and the control group. The eligibility criteria are stated above. The surveys will be carried out in all living areas of the respective nursing homes.

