Thirdly, empirical data will be collected in one living area of each nursing home of the intervention group in an observational study (‘shadowing’). The methodology was developed in the first PeBeM study and described in the final report [15]. The three elements of the data collection method are described in the background section. To assess actual-target differences (and their changes from t_0_ to t_1_), the shadowing data will be analyzed about (i) the number of interventions provided, (ii) the duration of the interventions provided, and (iii) the extent of qualification fitting. The determination of the respecting values is shown in Table 3.

**Table 3 Tab3:** Determination of actual and target data of care provision in the shadowing

Information provided in the data	Determination of the actual value	Determination of the target value	Involved Determiner
**Number** of provided interventions	Electronic time stamp while shadowing	1. DIP	1. Members of the study team qualified as a nurse
		2. Shadowers assessment	2. Shadowers
**Duration** of the provided interventions	Electronic time stamps while shadowing	Shadowers assessment	Shadowers
Extent of **qualification fitting**	Automatic electronic documentation while shadowing (data link in software between nursing staff and QL)	1. Software derives automatically from BI	1. Assessors and evaluators on behalf of the LTC insurance funds
		2. Software derives automatically from DIP (if additional information was registered)	2. As nurse-qualified members of the study team determine QL requirements individually

Fourthly, a partly standardized online questionnaire will be developed to assess the shadower's perception of the cooperation and communication structures within the nursing homes. The survey will be created based on experience from the PeBeM1 project.

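### Only intervention homes undergo the PeBeM data collection, so any net change it causes in survey scores between t0 and t1 is counted as intervention effect

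*Protocol article*

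**What the plan says.** All references are to the protocol article.

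- **Who is measured how.** Summative evaluation says: "The control group undergoes the surveys of the summative evaluation but not the shadowing nor the two intervention measures". Study design and participants gives the reason, "as the shadowing of the control group was regarded as too resource-intensive".
- **What the shadowing involves.** Summative evaluation points back to the PeBeM method: "The three elements of the data collection method are described in the background section". The section on the PeBeM data collection method lists the elements. The first is "Compiling a new assessment of the need for LTC", done by external assessors. In the second, scientists of the study team and "nurses from the respective nursing homes tailor an individual DIP for every resident". The third is the shadowing itself: "The care provision is observed in the nursing home for about one week", with each staff member "accompanied by a data-collecting shadower (also qualified nursing staff) on a one-to-one basis". The shadower also records care that was omitted or unnecessary.
- **Where and when.** One living area per intervention home, at t0 and at t1, one year apart.
- **Where the resident surveys go.** In both groups, "The surveys will be carried out in all living areas of the respective nursing homes". The paragraph on the online staff survey does not mention living areas.
- **What counts as intervention.** The section on application of the concept defines it as increased staffing plus organizational and personnel development. The PeBeM data collection is not listed.
- **How effects are estimated.** Study design and participants assigns quality of care and job satisfaction to a difference-in-difference between 10 and 10 homes. Limitations mentions the single shadowed area only with regard to transferability.

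**The concern.** Difference-in-difference removes stable differences between the groups and trends they share. It cannot remove an exposure that only one group receives and whose effect changes between the waves. The PeBeM data collection is such an exposure, and it is not passive. The home's own nurses help to set out each resident's care needs, external assessors re-examine those needs, and an outside nurse follows staff and notes gaps. This could plausibly change care, how residents rate it, or how staff answer questions on stress and time management.

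If such an effect differs between t0 and t1, the survey comparison attributes the difference to staffing and reorganization. The direction is open. Better care after the planning would favour the intervention; a favourable reaction that is stronger at t0 than at t1 would count against it. The results are meant to inform a national rollout, so it is worth knowing whether the survey contrast depends on the shadowed area.

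**Working it through.** The article states no sample size, effect size or number of living areas for this comparison, so there is no figure to reproduce. The check is algebra on the contrast.

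**Inputs**
- Data collection in intervention homes only, one living area each, at t0 and t1 (Summative evaluation).
- Resident surveys in all living areas of both groups (Summative evaluation).
- s, the share of intervention-arm respondents in the shadowed area: not given. Assumed 1/4, 1/3 and 1/2, which correspond to four, three and two living areas of equal size.
- m0 and m1, the effects of the data collection on those respondents' scores at t0 and t1: not given.

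**Formula, with no spill-over to other areas**
- Change in intervention homes = trend + intervention effect + s × (m1 − m0)
- Change in control homes = trend
- Difference-in-difference = intervention effect + s × (m1 − m0)

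**Cases**
1. Equal effect at both waves (m1 = m0): bias = s × 0 = 0. A reaction to the observation week that recurs identically at t1 falls here, if survey and shadowing follow the same order each time.
2. Survey before shadowing at t0 (m0 = 0), with an effect m present at t1: bias = s × m. For s = 1/4, 1/3 and 1/2 this is 0.25m, 0.33m and 0.50m. A lasting effect of the t0 planning has nothing at t0 to offset it.
3. Larger effect at t0 than at t1 (m0 > m1): the bias has the opposite sign to the effect. A favourable measurement effect then makes the intervention look weaker.

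**Illustration on an SD scale.** Assume a net change m1 − m0 of 0.1 to 0.2 SD. The bias runs from 0.25 × 0.1 = 0.025 SD to 0.50 × 0.2 = 0.10 SD. Every input is an assumption, and the shift must be read as the change between waves, not as the effect at one wave.

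**Spill-over.** Let a fraction k of the effect reach respondents in the other areas.
- All areas: bias = [s + (1 − s) × k] × (m1 − m0)
- Shadowed area excluded: bias = k × (m1 − m0)
- Difference between the two analyses = s × (1 − k) × (m1 − m0)

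With k = 0, exclusion removes the bias. With k = 1, both analyses carry the full net change and agree with each other. Agreement between them is therefore reassuring only if spill-over is limited.

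**The case against.** The strongest reply has five parts.

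1. **Repetition and dilution.** The data collection is done at both waves and in one area per home, so much of any effect may cancel or be diluted. This stands. A reader might infer that the whole measurement effect passes into the estimate; the design does not support that, because only s × (m1 − m0) does. What does not follow is that the term is zero: nothing in the article secures m1 = m0.
2. **Carry-over is conjecture.** The daily plan is described as covering the data collection period, and the article does not say that plans or ratings stay in use. This stands as a reason not to claim a size. It does not rule out an effect, since the home's nurses take part in the planning.
3. **The package already involves much contact.** Intervention homes alone also have inspections, competency assessments and fortnightly interviews. The final concepts are to include a standardized census of a home's actual status. So leaving out one living area would not isolate staffing plus reorganization. A reader might also infer that nothing like this measurement would exist after rollout; the article does not support so flat a statement, although it does not mention one-to-one shadowing for the rollout.
4. **Shadowed and other areas may differ.** The article does not say how the area is chosen, and staff may work across areas. This stands, so a contrast between areas is not a clean test.
5. **Details belong elsewhere.** Survey order, area codes and sensitivity analyses may be in the full protocol or analysis plan. Their absence from the article is accordingly not the point. The point is the stated asymmetry, combined with a limitations section that treats the single shadowed area only as a matter of transferability.

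**Conclusion.** The point holds in limited form. The survey difference-in-difference estimates the intervention effect plus s × (m1 − m0). For an assumed s of 1/4 to 1/2, that is 0.25 to 0.50 of the net change in the measurement effect between waves, if there is no spill-over. It reaches the full net change only if the effect spreads through the whole home. The article fixes neither s, nor the net change, nor its sign, so 0.025 to 0.10 SD is an illustration and not an estimate.

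Two stronger readings should be avoided. The asymmetry does not make the controlled comparison invalid. Nor can the share s be carried over to staff, because the sentence on living areas concerns the resident surveys. The bias is probably modest, but checking whether the contrast depends on the shadowed area is cheap, and the plan already surveys the respondents needed.

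**What to change.** - Record on each resident questionnaire in intervention homes whether it comes from the shadowed living area. Do the same for staff questionnaires where staff can be assigned to an area.
- Report the survey difference-in-difference with all areas and, as a sensitivity analysis, with the shadowed area excluded.
- Keep the same order of survey and shadowing at t0 and t1, and state it. Surveying first avoids reactions to the observation week but sets m0 to zero, so it must not be presented as removing carry-over from t0.
- Treat the contrast between shadowed and other areas within intervention homes as supportive only.
- Name the measurement effect under Limitations. This applies especially to the publicly reported indicators and external audits, which are reported per home and which an area code cannot reach.

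**Cost.** One code, one repeated analysis and a coding rule for staff who work across areas; no extra survey wave or respondents. The restricted analysis loses the shadowed respondents, a quarter to a half of the intervention arm under the assumed shares, and so is less precise. Spill-over would remain in it.
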